**Inclusion/Exclusion Criteria for Baseline Phase**

Inclusion:

- Aged 25 – 39 years
- Resident of the study village - has been living in the physical structure identified during the enumeration and who has been eating together in the same household.
- Intends to continue living in the village for the next 9 months (which is the estimated duration of data collection).
- Gives written consent to participate in the study and the interventions.

Exclusion:

- Outside the age range of 25-39 years
- Non-resident of study villages
- Intends to relocate from the study village within the next 9 months
- Declines *to consent to participate in the study or the interventions*

**Maintaining confidentiality**:

The RAs enrolling participants in the households will have access to the participant unique ID number because they will be responsible for assigning the numbers. However, the RAs at the clinics where participants go for circumcision will not have access to the Master Log; instead they will call the Data Officer in charge the Master Log to confirm participant’s identity. Data Clerks will also have access to the participant unique ID number during data entry. All data will be collected by trained staff and kept under lock and key, accessed by designated study staff only. As described on page 20, under Phase 1: Household Enumeration, the components of the Participant Unique ID number have been systematically mixed in order to maintain participants’ privacy.

Once they complete their roles, household RAs assigning the participant unique ID numbers and Data Clerks entering the information on the data base will not have further access to participants’ personal information. Clinic-based RAs who will be confirming identity of participants will not have access to the Master Log – they will verify identity of participants by calling the Data Officer in-charge of the Master Log (Appendix 14) at the head office.

# PHASE 4: IMPLEMENTING THE INTERVENTIONS

The study has four intervention arms: Inter-Personal Communications (IPC), Dedicated Service Outlets (DSOs), a combination of IPC and DSO (IPC+DSO), and Control. We have described here below how each of the interventions will be implemented.

**Study Arm 1: Inter-personal communications (IPC) intervention:** We will advertise for interested behavioral counselors, clients from our VMMC program, community health workers, and other community recruiters (e.g. female partners, circumcised men), to be trained as VMMC interpersonal communicators (aka Research Assistants - RAs). We will add on to the list other preferred recruiters suggested by participants during the Formative Phase (sub-study 1). They will be trained for 5-6 days on the following contents: highlights of the observational studies prior to the MC clinical trials, the clinical trials design and results, how VMMC works to reduce HIV, operational research alongside VMMC rollout, and VMMC uptake in Kenya disaggregated by age. These will equip them with sufficient background information necessary to answer a wide array of questions that may arise during implementation of the interventions.

They will then be thoroughly trained on the barriers to and facilitators of VMMC among older men using information from previous studies as well as from the Formative Research phases of the study. The RAs will also be trained on and practice intervention implementation – how to approach potential participants in their households, how to deliver the messages, how to answer questions, and so on. After obtaining IRB approval, the trainees will participate in practical exercise where they will go out and put into practice the skills and share their experiences in a report-back session. This practical exercise will be in the form of role plays so that RAs get to practice with colleagues what they have learnt during training. A pre-post training evaluation exercise, as well as performance during practicals, will be used to assess competency and identify those qualified to be engaged as recruiters.

Recruitment Approach: Depending on participant’s availability, this phase can be conducted together with Phase 2 if the intervention tool (Appendix 6) has been approved, and done subsequent to verification of MC status; alternatively, another visit will be made if participants do not have time or if Appendix 6 has not been approved. If another visit is needed, we will visit every household with enrolled participants at a time when they are likely to be at home (with their spouses where applicable) to discuss VMMC using the demand creation tool (Appendix 16: *VMMC Demand Creation Tool kit*) as described in the next sub-section.

Participants in IPC or IPC/DSO Location will receive information on VMMC while those in DSO Locations will be informed about, and given directions to VMMC sites designated to older men. During consenting, participants will be informed that by consenting to be enrolled in the study, they are consenting to be assigned into one of the three intervention arms or control. Hence, by consenting to join the study they will also have consented to participating in the respective interventions. After delivering the intervention (whether at enrollment visit or a subsequent one), participants will be given a pre-designed referral coupon (Appendix 15: Referral Coupon) to take along when going for services. They will also be asked to memorize the serial number if possible. The RAs will be expected to return to the same households up to three times (within a period of three month) to reach those not found at home during the previous visit – this applies to both enrollment visit and the visit to deliver the intervention, if different from enrollment visit.

Delivery Process of IPC Intervention: We propose an approach whereby a trained RA (behavioral counselors, circumcised men, CHWs, or any other cadre of individuals identified during the formative phase(e.g. female partners, circumcised men) will meet older men in their households, and do the following: i) approach the person(s), introduce self as an RA from IRDO, develop rapport and request for time to discuss briefly about VMMC; ii) strike a conversation on reasons why they or their peers have not gone to be circumcised as well as reasons that would make them get circumcised, jotting down responses to guide the discussion. The responses will be written down in a notebook with carbonated duplicate pages per participant (**APPENDIX 44: DOCUMENTING DISCUSSION AT IPC AND IPC/DSO LOCATIONS**). The top page will be submitted for data entry and the copy will remain in the notebook. Only the Participant’s ID# (described on pg. 25), District, Location, Village and RA ID # will be indicated; iii) using the *Toolkit for Addressing Barriers and Facilitators to VMMC (Appendix 16)*, address each reported barrier carefully and completely, always ensuring the person(s) is/are engaged in the discussion (the goal is to pass correct and complete information in a relaxed and conversational manner); iv) revisiting each stated barrier and exploring what they now think about them after the discussion, explore whether the same barriers would still deter them/their peers from getting circumcised, and address any new or lingering concerns.

“Data collected from this exercise will first be coded by key themes, such as myths, misconceptions or misunderstandings. For each theme, we will obtain frequencies of mention; for example, for each misunderstanding, wrong length of time for sexual abstinence, wrong number of pain injections administered, wrong understanding of where injection is given or what gets surgically removed, etc. will be tallied. We will then document the extent of each misunderstanding by reporting the frequency and proportion of mention. We will link the Participant ID# to get his demographic data (age, education, marital status, and employment status) from **Appendix 2B: ENROLLMENT QUESTIONNAIRE AND CIRCUMCISION VERIFICATION AT BASELINE AND ENDLINE**. No personal identifiers will be collected or reported specifically for this activity.”

Moving on to the facilitators for VMMC, the RA will then pick each benefit/facilitator mentioned by the person/family members and reiterate their importance, ensuring sufficient and correct information is given. To conclude, the RA will encourage the men to seek VMMC and ask them to urge their family members and friends to also go for circumcision. The RA will leave behind a referral coupon (Appendix 15) indicating sites where VMMC is being offered in the neighborhood and contact information of team leaders in case of questions. Copies of *Appendix 17: ‘All You Need to Know About VMMC’ booklet* will be left with each person/family reached, for ongoing reference and to share with others.

While different RAs will reach out to potential participants to create demand for VMMC and make referrals to service provision sites, the effectiveness of each cadre of RA (behavioral counselors, CHWs, teachers, VMMC clients, etc) will be assessed through the number of referral coupons surrendered at the VMMC clinic after circumcision. Those who have forgotten/lost their referral coupons will be asked for the serial number of their referral coupon, which will be confirmed from the Tracking Log (Appendix 3A) and matched with the RA assigned to the respective Location and village.

**Study Arm 2: Designated service outlets (DSO) intervention** One of the concerns older men have expressed about going for VMMC services at current facilities is the fact that they are made to queue with age mates of their children.^23^ They find this embarrassing given VMMC is a private affair and one that touches on sexuality, an often taboo subject between parent and child in many African households.^26^ Also, because VMMC has been largely marketed as an HIV and STI prevention strategy, older men believe young people may perceive them as going for circumcision because they are promiscuous. To make older men feel comfortable going for VMMC, we plan to set up DSOs to serve men aged ≥25 years, exclusively.

Recruitment Approach and Delivery of the DSO Intervention: If not done at enrollment visit, the RAs shall visit every household with eligible men (uncircumcised, age 25-39 years) in Arm 2 to inform them about the availability of DSO sites in their neighborhoods. For participants in this arm, the RAs will describe DSOs as sites where services are offered exclusively to men aged ≥25 years. These will include designated health facilities (including private facilities) and designated days of the week in selected health facilities. They will also include providing services in the evenings and weekends, and through special mobile services targeting older men only. In all the DSO sites, participants will be served by male staff in the same age bracket.

Potential participants will also be informed that at DSO sites we will strive to shorten the waiting time to no more than three hours. A floating circumcision team will be called upon whenever there is a surge of participants, and we shall establish a system of rebooking participants who arrive late, or as soon as it is apparent that surgery cannot be done the same day. There will also be information that all other VMMC sites continue to serve all men regardless of age (i.e., including older men) while DSO sites will only serve men aged ≥25 years.

After describing the characteristics of DSO sites, the RA will share - both verbally and through a flyer (Appendix 18: DSO Sites and Location Information) - information on where to find DSO sites in the respective Location. If there are questions from participants, they will respond using: *All You Need to Know About VMMC* booklet (Appendix 17), the same way current recruiters do.

To monitor which questions are asked and how they are responded to, we have developed a monitoring tool (Appendix 19: Monitoring Form for Demand Creation Strategies) to document demand creation activities, and have included questions asked by participants. Staff will be trained on how to pass sufficient information using Appendix 17 without going into details contained in IPC. The monitoring tool will enable us to identify DSO and Control participants who may have received information that puts them close to IPC recipients. In addition, different group of RAs will be trained only on the intervention they will deliver, thus minimizing the chance that DSO RAs will have sufficient information on IPC to conflate the two during intervention delivery.

**Study Arm 3: Combined IPC and DSO interventions:** In selected Locations, IPC and DSO interventions (as described above) will be implemented concurrently. This will be done to determine the effect of both interventions delivered jointly compared to each delivered singly, and compared to no intervention.

Delivery Process of IPC+DSO Intervention: Activities and processes described under IPC and DSO will be replicated in these Locations/villages. The RAs will inform their participants about DSO sites and non-DSO sites in their neighborhoods, to allow people make a choice on where to go. Participants will be informed that services continue to be offered at all other facilities regardless of age. Copies of *Appendix 17: ‘All You Need to Know About VMMC’ booklet* will be left with each person/family reached in IPC+DSO sites, for ongoing reference and to share with others.

Participants aged 25-39 years in DSO and DSO+IPC Locations seeking services in non-DSO sites will be asked question 2 in Appendix 20 B (*What or who influenced your decision to come to this site while there are VMMC sites dedicated to men your age in this Location?*). The information will be useful in understanding reasons for preference for non-DSO sites yet DSO sites are available.

**Study Arm 4: Control/No Intervention:** One-quarter of participating Locations has been randomly assigned to the Control or No Intervention or ‘standard of care’ Arm. In these Locations, participants will only be reached with information on VMMC with reference to the ’*All You Need to Know About VMMC’* booklet (Appendix 17) at the time of enrollment.

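### The IPC discussion notes do not separate a man's own reasons from his peers' before the tally is linked to his demographics, and the reported proportion has no stated denominator

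*Protocol*

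**What the plan says.** The text is in Protocol Phase 4, Study Arm 1, under the delivery process of the IPC intervention. The assistant opens by asking for reasons that apply to the man or to people like him: "strike a conversation on reasons why they or their peers have not gone to be circumcised". On recording, it says: "The responses will be written down in a notebook with carbonated duplicate pages per participant" (Appendix 44). The identifying fields are the participant's ID together with the following: "District, Location, Village and RA ID # will be indicated". After the discussion the assistant goes back over the stated barriers and is to "explore whether the same barriers would still deter them/their peers from getting circumcised".

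For analysis, responses are coded into themes such as myths and misunderstandings. The counting rule is: "For each theme, we will obtain frequencies of mention". The summary is: "We will then document the extent of each misunderstanding by reporting the frequency and proportion of mention". The linkage is: "We will link the Participant ID# to get his demographic data", namely age, education, marital status and employment status, taken from the enrolment questionnaire (Appendix 2B).

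**The concern.** The question deliberately covers two sources, the man and his peers. That is a sensible way to open a conversation on a sensitive subject. The difficulty arises when the same notes become data. The page belongs to one man and carries his ID, and its contents are joined to his characteristics, yet some of what is written may describe other people.

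Two readings of the result are then open to error. One is the overall level: a reader of the report will naturally take the stated proportion as the share of older men who hold each misunderstanding. The other is the breakdown by age, education, marital or employment status, where a peer's belief would be counted under the participant's category. Separately, the text does not say what the proportion is a proportion of, nor whether a theme raised twice by one man counts once.

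At stake is a secondary descriptive result on which misunderstandings are common and in whom.

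**Working it through.** There is no figure in the plan to reproduce, so the check is mainly a comparison of texts.

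**1. Elicitation.** The opening question joins own and peer reasons. The later step that revisits barriers ("explore whether the same barriers would still deter them/their peers from getting circumcised") joins them again. Others in the household may also speak: for facilitators, "the RA will then pick each benefit/facilitator mentioned by the person/family members".

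**2. Recording.** The unit is the participant's page. The fields named are the participant ID, district, Location, village and assistant ID. No field or mark for the source of a reason is described. Appendix 44 itself is not among the documents.

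**3. Counting.** The unit is the mention, by theme. Neither a once-per-man rule nor a denominator is stated.

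**4. Linkage.** The page is joined to the man's own demographic data. Nothing restricts the join to reasons that are his.

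**5. What can be recovered later.** The denominator and the once-per-man rule could be settled in an analysis plan, because pages carry an ID. The source of each reason could not: if it is not noted during the discussion, it is lost.

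**6. Reach.** The discussion is held in the IPC and IPC+DSO arms. From Table 2, that is 11 + 12 = 23 of 45 Locations. At the planned 1,233 men per arm (Sample size Determination), it is 2 × 1,233 = 2,466 men.

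**7. Illustration with assumed inputs.** None of these inputs comes from the protocol; they only show how each gap works. Suppose 100 men have a completed page, 40 of them raise a given misunderstanding once each, and all themes together produce 200 to 400 mentions.

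- *Denominator.* Share of men raising it: 40/100 = 40%. Share of all mentions: 40/400 = 10% to 40/200 = 20%. These are different quantities, and the text does not say which is meant.
- *Source.* If between none and half of the 40 men are reporting peers only, the share who hold the misunderstanding themselves is (40 − 0)/100 = 40% down to (40 − 20)/100 = 20%.
- *Breakdown.* Take two demographic groups of 100 men in each of which 20 hold the belief themselves. If 20 further men in one group report it of peers only, and none do in the other, the tallies are (20 + 20)/100 = 40% and 20/100 = 20%. The difference comes entirely from peer reports.

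**The case against.** The strongest reply has five parts.

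- *Many mentions will be the man's own.* The question asks for his reasons too. The protocol's examples (abstinence period, number and site of injections, what is removed) are factual errors that the speaker would often hold himself. This stands. A reader might infer that the tally does not describe the participant at all; the text does not support that. It shows only that an unknown share of mentions may belong to others.
- *A proportion of men can still be computed.* Pages are kept per participant with an ID, and the stated proportion may mean just that. This also stands. A reader might infer that the denominator is all mentions, so that talkative men weigh more. The protocol does not say so; the denominator is undefined, not wrongly fixed. Taken alone, that could be left to an analysis plan, which is not shown.
- *Appendix 44 is not shown.* It may already separate self from peer. The point is therefore conditional on the form, although the protocol's description of it mentions no such mark.
- *Men's reasons are collected elsewhere.* The enrolment questionnaire (Appendix 2B) asks for top reasons for going or not going. At endline, men who report not having gone are asked why and rank up to three reasons (Appendix 2D). This limits the consequence, but neither use of those forms corrects the IPC tally or its linkage.
- *The tally does not shape the messages.* A reader might suppose that it does. The protocol assigns that role to the formative focus groups and interviews, which update the toolkit before IPC delivery. The stated use of the IPC notes is documentation only.

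What remains is the joint question combined with the unrestricted link to the man's demographics.

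**Conclusion.** The point holds in a limited form. As described, the notes mix own and peer reasons, and the summary has no stated denominator. The reported extent of each misunderstanding therefore cannot be taken as its prevalence among participants, and a breakdown by age, education, marital or employment status can assign peers' beliefs to the participant.

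The size is unknown: it depends on the share of mentions that concern peers only and on the denominator eventually used, and the documents give neither. It would be too strong to say that the breakdown describes the wrong people altogether. The conclusion assumes that Appendix 44 holds no self/peer mark beyond what the protocol describes.

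This is a secondary descriptive analysis in two of the four arms. The primary comparison of VMMC uptake and the sample size are not touched. It is a cheap improvement, not a threat to the trial's main result.

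**What to change.** Keep the conversational question as it is, and change the recording and the tabulation:

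1. On the Appendix 44 page, unless it already does so, mark each response as self or peer when it is written down.
2. Count each theme at most once per man.
3. Report each theme as a percentage of men with a completed discussion page, and state that denominator in the protocol text.
4. Link only self responses to the demographic data from Appendix 2B.
5. List peer responses in a separate table, described as what participants report of others.

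The cost is one extra mark per response during the discussion and a revised table. The self/peer mark must be in place before the discussions start, because it cannot be reconstructed afterwards; the other items can be settled at analysis.
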